### Prior and Concomitant Medication

Participants will receive clear instructions not to take any medication other than the trial drugs for any condition without prior consultation with the investigators. The investigator will advise participants to promptly report any additional signs, symptoms, or unusual occurrences and to seek guidance accordingly. Additionally, the investigator will diligently document any other medications taken by the participants for comprehensive recordkeeping.

### Rescue Medication

Permission will be given for the use of rescue medication for alleviating any emergency condition as per the discretion of the investigator. It will be documented in detail in the CRF.

## Results

As of December 2024, a total of 79 patients have been enrolled. Data analysis should be completed by February 2026. The study will be reported following standard guidelines for reporting randomized controlled trials. Clinical results will be disseminated to the public through conference presentations and peer-reviewed publications in a relevant, open-access journal.

## Discussion

### Conclusion

Ayurveda scholars correlate *Raktapradara* with menorrhagia (National Ayurveda Morbidity Code: EL-4) based on the similarities in causes, clinical features, and treatment. This paper describes the protocol for the Ayurvedic management of menorrhagia. We undertook a randomized controlled trial to objectively assess the efficacy of Ayurvedic treatments for the management of menorrhagia and compared it with standard conventional treatment. The changes are assessed objectively by using the PBAC score and MIQ as the outcomes for participants with menorrhagia.

Studies have demonstrated promising results of some Ayurvedic interventions for managing *Raktapradara*. With this study, we aim to observe the effectiveness and safety of Ayurvedic management using the formulations of *Ashokarishta* and *Trinakantamani pishti* in reducing symptoms associated with menorrhagia, such as HMB. If beneficial, this study could contribute significantly to integrative approaches for managing menorrhagia.

### Strengths and Limitations

The strengths of this study include its randomized design and the inclusion of enough participants to allow for adequate statistical power for subgroup analyses. This study uses the PBAC score and MIQ, which are well-validated instruments to assess menorrhagia.

One potential limitation of this study is that the investigators were aware of the participants’ group assignment, and therefore, bias in favor of any particular group cannot be excluded. However, every effort was made to ensure blinding of the participants during the group allocation. An independent evaluator blind to study conditions was responsible for administering all study measures. The protocol may also serve as a reference for the planning of similar clinical trials.

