### Sample Size

To calculate the sample size, we anticipated a difference of 70 units in average PBAC score after treatment between the two groups (*Trinakantamani*
*pishti* along with *Ashokarishta* vs tranexamic acid tablet), with an SD of 137 units based on the results of the previous study [14]. With 95% confidence level (α=.05) and 80% power, the number of patients to be enrolled in the study was calculated using the following formula:

where *Z*_1 – α/2_=1.96, *Z*_1 – β_=0.84, σ=137, and δ=70.

Expecting a dropout rate of 15%, the number of patients is estimated to be 60 + 9 = 69. Thus, approximately 70 patients should be enrolled in each group.

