### Randomization and Allocation

A randomization chart will be generated with the help of computer-generated random numbers. Participants will be randomized in a ratio of 1:1 to either of the two groups. The randomization schedule will be strictly controlled and remain with the biostatistician/data analyst. Sequentially numbered, sealed, opaque envelopes will be used to conceal the allocation.

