### Statistical Methods

Continuous variables will be presented as mean, SDs, medians, and ranges. Categorical variables will be summarized with frequencies and percentages. When inferential analyses will be conducted for continuous variables, they will be tested for normality. Nonparametric methods will be used to compare nonnormal data. Within-group comparison will be done using a paired *t* test (1- or 2-tailed, as suitable), while between-group comparisons will be done using an independent sample *t* test (1- or 2-tailed, as suitable) for the data following normal distribution. Nonnormal data within the group will be compared using the Wilcoxon sign rank test, while between groups comparison will be done by using the Mann-Whitney *U* test. Categorical data between groups will be compared using the chi-square or Fisher exact test. A 2-sided *P* value of <.05 will be considered statistically significant. Per-protocol and intention-to-treat analyses will be carried out at the end of the study. All data will be analyzed using Stata (version 16.1; Stata Corp).

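### The claim of adequate power for subgroup analyses is not supported by the sample size calculation, which reaches 80% only for the overall PBAC comparison and uses every evaluable patient to do so

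*Protocol article*

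**What the plan says.** In the Discussion of the protocol article, under Strengths and Limitations, one of the named strengths is "the inclusion of enough participants to allow for adequate statistical power for subgroup analyses". No subgroup, subgroup effect or power figure accompanies it.

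The number of participants is justified only under Methods, Sample Size. There, "we anticipated a difference of 70 units in average PBAC score after treatment between the two groups", "with an SD of 137 units based on the results of the previous study". The error rates are given as "With 95% confidence level (α=.05) and 80% power". The result is 60 per arm before dropout: "Expecting a dropout rate of 15%, the number of patients is estimated to be 60 + 9 = 69", so that "approximately 70 patients should be enrolled in each group". Randomization and Allocation fixes a 1:1 ratio. Statistical Methods sets a two-sided 5% significance level and describes no subgroup or interaction test.

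**The concern.** A trial sized to give 80% power for one overall difference has, by construction, less than that for the same difference in part of its population, unless it was deliberately enlarged. The Sample Size section shows no such enlargement: the only addition to the 60 per arm is for dropout. The statement in Strengths and Limitations therefore credits the design with a property that its own inputs do not give it.

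What is at stake is how later subgroup results are read. A reader told that subgroup power is adequate may take a non-significant subgroup result as evidence of no effect, or a difference between subgroups as more reliable than it is. The same section offers the protocol as a reference for planning similar trials, so the claim could also be carried into other designs.

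**Working it through.** **Inputs from the protocol.** Difference δ = 70 PBAC units, SD σ = 137, Z values 1.96 and 0.84, 60 evaluable and about 70 enrolled per arm (all Sample Size); 1:1 allocation (Randomization and Allocation); two-sided 5% level (Statistical Methods).

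**Assumptions, because the protocol gives no subgroup figures.** Subgroups are balanced across arms; the SD is 137 within each subgroup; the effect is 70 units in the subgroup tested; for the interaction, the two subgroup effects differ by 70 units. The split is varied.

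**Step 1: reproduce the planned number.** The formula is not legible in the text at hand, but the standard one for two means gives

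n = 2 × [σ(1.96 + 0.84)/δ]² = 2 × (137 × 2.80/70)² = 60.06 per arm,

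which matches the stated 60. The dropout step, 60 × 1.15 = 69, also matches.

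**Step 2: overall power.** SE = σ√(2/n) = 137 × √(2/60) = 25.0. Power = Φ(70/25.0 − 1.96) = 79.9% (79.3% with the t distribution). The 80% is used up by the whole evaluable sample. Because SE rises as n falls, any subset of the 60 has lower power at 70 units and SD 137, whatever the subgroup is.

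**Step 3: power within a subgroup, 60 evaluable per arm.**
- 30 per arm: SE = 137 × √(2/30) = 35.4; power = Φ(70/35.4 − 1.96) = 50.8% (t-based 49.5%).
- 15 per arm: SE = 137 × √(2/15) = 50.0; power = 28.8%.
- 45 per arm: SE = 137 × √(2/45) = 28.9; power = 67.9%.

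In a half-size subgroup, 80% power needs a difference of 2.80 × 35.4 = 99 units.

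**Step 4: power for the interaction.** SE = σ√(2/n₁ + 2/n₂). For an equal split, SE = 137 × √(2/30 + 2/30) = 50.0 and power = Φ(70/50.0 − 1.96) = 28.8%. For 25/75, SE = 137 × √(2/15 + 2/45) = 57.8 and power = 22.7%. With an equal split, 80% power needs an interaction of 2.80 × 50.0 = 140 units, twice the planned effect. A 70-unit interaction would need about 4 × 60.06 = 240.2, that is 241 per arm.

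**Step 5: range.**

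| Evaluable per arm | Split | Power in smaller / larger subgroup | Power for 70-unit interaction |
|---|---|---|---|
| 60 | 50/50 | 51% / 51% | 29% |
| 60 | 33/67 | 36% / 63% | 26% |
| 60 | 25/75 | 29% / 68% | 23% |
| 70 | 50/50 | 57% / 57% | 33% |
| 70 | 33/67 | 41% / 70% | 30% |
| 70 | 25/75 | 33% / 74% | 26% |

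The 70-per-arm rows assume no dropout at all. The abstract's 20% dropout would leave 70 × 0.80 = 56 per arm, which can only lower the figures for 60.

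**The case against.** The strongest reply has four parts.

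- **The subgroup figures are not the protocol's.** It gives no split, subgroup SD, subgroup effect or interaction size. A half-size subgroup would have 80% power for about 99 units, or for 70 units if its SD were about 137/√2 = 97. This stands as a limit on the numbers: a reader might infer that 50% and 29% are fixed properties of the trial, and the protocol does not support that. They are illustrations. It does not rescue the claim, because nothing in the protocol proposes a larger subgroup effect or a smaller subgroup SD.
- **The Sample Size section is silent on subgroups and its arithmetic is sound.** This stands. A reader might infer a calculation error; there is none, since 60 reproduces. The fault is in the Discussion statement, which that calculation cannot support at its planned effect.
- **The calculation covers PBAC score only.** For duration of bleeding, attainment of normal blood loss and the Menorrhagia Impact Questionnaire the protocol gives no SD or effect, so subgroup power for those cannot be judged either way. This also stands, and it means that the claim has no support there either.
- **No subgroup analysis is planned in the text.** Statistical Methods describes none, so no planned test, sample size or procedure is affected. A reader might go further and infer that a planned analysis is compromised, or that most subgroup findings would be noise. Neither follows: there is no such planned analysis in the article, and low power alone does not establish the second. That no subgroup is named is not an error in itself, because definitions may sit in a full protocol or analysis plan that is not shown.

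An unseen analysis plan could define subgroups, but it could not make the statement true at the planned effect, because the number of participants is fixed here.

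**Conclusion.** The statement is wrong as written and should be corrected. That subsets of the 60 evaluable per arm fall below 80% power rests only on the protocol's own δ = 70, SD = 137 and two-sided 5% level, with that same effect and SD applied in the subset. How far below depends on the assumptions listed in the working.

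With zero dropout, a subgroup of 60 out of 70 per arm would reach about 80%, but the remaining 10 per arm would have about 21% (SE = 137 × √(2/10) = 61.3; Φ(70/61.3 − 1.96)). No split examined powers both parts.

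The consequence is confined to interpretation. The overall comparison remains powered as the protocol states.

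**What to change.** In Strengths and Limitations, delete the subgroup-power claim. Alternatively, replace it with a sentence to this effect: *the trial is sized only for the overall between-group comparison of PBAC score, and any subgroup analysis is exploratory.*

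The cost is one sentence and one claimed strength. Sample size, design, analysis and conduct are unchanged. The change is best made before results are interpreted; the article expects data analysis to be complete by February 2026.

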## Abbreviations

CONSORT: Consolidated Standards of Reporting Trials
CRF: case report form
HMB: heavy menstrual bleeding
MIQ: Menorrhagia Impact Questionnaire
PBAC: Pictorial Blood Loss Assessment Chart
SPIRIT: Standard Protocol Items: Recommendations for Interventional Trials
